## Abstract

**Background:**

Calcineurin inhibitor induced nephrotoxicity contributes to late allograft failure in kidney transplant patients. Evidence points towards aldosterone to play a role in the development of fibrosis in multiple organs. Animal studies have indicated a beneficial effect of mineralocorticoid receptor antagonists preventing calcineurin inhibitor induced nephrotoxicity. Only few studies have explored this effect in humans. The objective of this study is to evaluate the effect of spironolactone on glomerular filtration rate and fibrosis in kidney transplant patients.

**Method:**

Prospective, double-blind, randomized, clinical trial including 170 prevalent kidney transplant patients. Patients are randomized to spironolactone 25–50 mg/day or placebo for three years. Primary outcome is glomerular filtration rate evaluated by chrome-EDTA clearance. Secondary outcomes are 24-h protein excretion, amount of interstitial fibrosis in renal allograft biopsies, and cardiovascular events. As an exploratory outcome, we aim to identify markers of fibrosis in blood and urine.

**Discussion:**

Long term allograft survival remains a key issue in renal transplantation, partly due to calcineurin inhibitor induced nephrotoxicity. Evidence from animal- and small human studies indicate a beneficial effect of mineralocorticoid receptor antagonism on renal function and fibrosis. This study aims to test this hypothesis in a sufficiently powered randomized clinical trial. Results might influence the future management of long term allograft survival in renal transplantation.

**Trial registration:**

ClinicalTrials.gov identifier (05/17/2012): NCT01602861. EudraCT number (05/31/2011): 2011–002243-98.

## Background

### Background and rationale

The introduction of calcineurin inhibitors (CNI) cyclosporine and tacrolimus as part of immunosuppressive regimens in kidney transplantation has significantly improved short term allograft survival and function [1, 2], but continuous exposure to CNI can result in renal fibrosis ultimately leading to chronic allograft failure. CNI nephrotoxicity is partly caused by vasoconstriction, thereby reducing renal blood flow and inducing oxidative stress, but also CNI directly increase the pro-fibrotic factor transforming growth factor β (TGF-β), apoptosis and macrophage infiltration [3]. Early reports indicated a prevalence of chronic CNI nephrotoxicity of up to 100% after 10 years of cyclosporine treatment [4], although a recent follow up has indicated less nephrotoxicity of modern, tacrolimus-based immunosuppressive protocols [5]. Nevertheless, improving long term allograft function remains a key challenge in renal transplantation.

The mineralocorticoid hormone aldosterone contributes to deleterious pro-fibrotic processes in several organs, including the kidneys [6, 7]. Aldosterone exerts its effects partly via the intracellular mineralocorticoid receptor (MR). Signaling via the MR regulates salt- and water balance, but also prompts inflammation, vasoconstriction and oxidative stress, which ultimately leads to tissue fibrosis [7]. Several large scale studies in congestive heart failure have highlighted the beneficial effect of MR antagonism on survival [8, 9] – partly explained by decreased myocardial fibrosis [10]. In chronic kidney disease, MR antagonism has shown beneficial effects reducing proteinuria, but no study has been sufficiently powered to investigate the effect on kidney function [11]. Evidence from animal models of CNI nephrotoxicity suggests a beneficial effect of MR antagonism on renal blood flow [12, 13], glomerular filtration rate (GFR) [12–18] and renal fibrosis [15–18].

Only a few studies have explored the potential of MR antagonism in kidney transplant recipients. A recent randomized clinical trial included 24 pediatric kidney transplant patients with biopsy-proven chronic allograft nephropathy and did not find a significant effect of eplerenone for 24 months versus placebo regarding GFR, proteinuria and fibrosis. The study was, however, underpowered [19]. One open-label study of 11 kidney transplant patients found significantly reduced levels of proteinuria after 6 months of spironolactone treatment despite unaltered blood pressure [20]. These findings were supported by a retrospective cohort study of 140 proteinuric kidney transplant patients concurrently treated with spironolactone [21]. Additionally, it has been shown that eplerenone given one day before and three days after the transplantation reduces markers of oxidative stress related to ischemia/reperfusion [22]. Hence, current evidence points towards beneficial effects of MR antagonism in kidney transplant patients. This remains to be confirmed in a sufficiently powered prospective trial.

### Objectives and design

The SPIREN trial is an investigator initiated nationwide, multicenter, randomized, double-blind, placebo-controlled clinical trial designed to test the hypothesis that addition of the MR-antagonist spironolactone to standard therapy in prevalent kidney transplant patients will improve long term kidney function and reduce allograft fibrosis.

## Methods

One hundred seventy kidney transplant patients will be included from four Danish hospitals covering all Danish renal transplant centers (Odense, Copenhagen and Aarhus). Patients are recruited from outpatient clinics in the Departments of Nephrology at Odense University Hospital, Kolding Hospital, Rigshospitalet, Copenhagen and Aarhus University Hospital, respectively. Eligibility criteria are listed in Table 1.

**Table 1 Tab1:** Eligibility criteria

Inclusion criteria	Exclusion criteria
Age > 18 years	Former intolerance of spironolactone
Tacrolimus/cyclosporine treatment	Potassium binder or digoxin treatment
Proteinuria < 3 g/day	Pregnancy or planned pregnancy
Creatinine clearance ≥30 mL/min	Clinically relevant organic, systemic or psychological disorder
Plasma potassium < 5.5 mmol/L	Expectation of non-compliance
Negative pregnancy test at inclusion for women of childbearing potential and adequate contraception throughout the trial	

Wide eligibility criteria have been chosen to obtain a high generalizability of the results. This study includes renal transplant patients with a stable kidney function at the time of inclusion. Even in stable patients, a gradual deterioration of renal function is expected. Previous studies have found an average rate of decline of glomerular filtration rate in of 1–3 mL/min/year [23–26]. Hence, we chose a follow up of 3 years.

Patients are randomized 1:1 to spironolactone (Spirix®) or placebo for three years. Initial dosage is 25 mg once daily, which is doubled after three months, if tolerated well. At inclusion and yearly hereafter a standard workup is performed including chrome-EDTA clearance, 24-h urine collection, electrocardiogram, 24-h ambulatory blood pressure measurement and blood- and urine samples (Fig. 1). Anonymized samples are stored at − 80 °C until analyses. In a subgroup (*n* = 50) graft biopsies will be performed at inclusion and after two years. All registrered variables are listed in Table 2.

**Fig. 1 Fig1:**
[figure not shown]
Participant timeline

**Table 2 Tab2:** All registered variables

Baseline	Every 3 months	Additionally at 0, 1, 2, 3 years		0 and 2 years (*n* = 50)
Date of birth Sex Height Smoking Number of pack years Primary kidney disease Previous dialysis Transplantation date Number of previous transplantations **Comorbidity** Apoplexia Myocardial infarction/cardiac revascularisation Heart failure Hypertension Diabetes Other	**Current medication** **Symptoms** Dizziness Fainting Shortness of breath Gynecomasty Impotence Others **Objective findings** Blood pressure (systolic) Blood pressure (diastolic) Pulse Bodyweight **Blood samples** Sodium Potassium Creatinine **Adverse events** **Compliance to study drug**	**Objective findings** Heart stethoscopy Lung stethoscopy Edema ECG Chrome-EDTA clearance **Blood samples** CRP Total cholesterol HDL LDL Triglyceride Markers of fibrosis **24 h urine sample** Creatinine clearance Proteinuria U-sodium U-potassium Markers of fibrosis	**Ambulatory blood pressure** SBP DBP SBP-day SPB-night DBP-day DBP-night Average pulse	**Kidney biopsy** Amount of fibrosis (%) Banff-score

*ECG* Electrocardiogram, *CRP* C-reactive protein, *HDL* High density lipoprotein, *LDL* Low density lipoprotein, *SBP* Systolic blood pressure, *DBP* Diastolic blood pressure

Side effects, adverse events and compliance to the study drug are evaluated at project visits every three months. Compliance is evaluated by counting tablets.

### Outcome

Outcomes are summarized in Table 3.

**Table 3 Tab3:** Study outcomes

Primary endpoint	Secondary endpoints
Chrome-EDTA clearance	24 h urinary protein excretion
	Renal fibrosis (morphology)
	Cardiovascular events
	Biomarkers of fibrosis in tissue, blood and urine

The primary endpoint is renal function evaluated by chrome-EDTA clearance, in which glomerular filtration rate is calculated from the area under the plasma clearance curve after a single intravenous doses of ^51^CrEDTA. Plasma concentrations of ^51^CrEDTA can be determined with a single blood sample by measuring residual radioactivity 4 h after the injection or by multiple samples 4, 5 and 6 h after the injection. For centers using a single blood sample after 4 h, an additional blood sample is performed 24 h after the injection in male patients with plasma creatinine ≥200 μmol/L and female patients with plasma creatinine ≥150 μmol/L. In repeat chrome-EDTA clearance measurements the coefficient of variation is 8–10% [27].

Secondary endpoints include 24-h urinary protein excretion, cardiovascular events (death, myocardial infarction, stroke or peripheral arterial thrombosis) and renal fibrosis. For the latter, Masson Trichrome stained sections of kidney allograft biopsies will be used for measuring Banff chronicity scores and calculating morphologic fibrosis by point counting. Point counting provides a quantitative and reproducible estimation of the extent of fibrosis [28]. In brief, the software systematically selects sections of renal cortex and superimposes a grid on a computerized image. The extent of fibrosis is determined by counting the fraction of intersection points that overlie fibrotic areas relative to normal tissue. Limitations of both Banff scoring and point counting are the risk of sampling error as well as the somewhat subjective evaluation of fibrosis. In this study all biopsies will be reviewed by the same pathologist to avoid inter-observer variability.

As an exploratory outcome we aim to identify possible biomarkers of fibrosis in blood and urine. Kidney fibrosis is currently diagnosed by renal biopsy. Besides being time-consuming, it is an invasive procedure and as such, it implies a risk of complications including bleeding, pain and infection. Hence, much effort has gone into identifying non-invasive markers of fibrosis in blood or urine. The fibrotic process is a cascade of factors including inflammation, tissue hypoxia and various pro-fibrotic cytokines and growth factors [29]. Animal studies of MR antagonism in CNI nephrotoxicity have identified several markers involved in the fibrogenic process that were regulated by MR antagonists [30]. Simultaneous plasma−/urine samples and renal biopsies allow for the possible identification of non-invasive markers of fibrosis. Further, studies of markers in blood and urine might contribute to our understanding of the molecular mechanisms of MR antagonism. Specific markers of interest will be defined when all samples have been obtained.

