### Safety

Plasma potassium and -creatinine levels are monitored closely at initiation of therapy and after any dose adjustment. Sustained potassium levels > 5.8 mmol/L will result in reduction of dosage to 25 mg per day. In case of hyperkalemia on 25 mg per day, the patient will be withdrawn from the study. Potassium binding resins will only be used to handle cases of acute hyperkalemia, thus chronic treatment with resins is not allowed. Hyperkalemia is registered as an adverse event in case of an absolute increase of > 1.5 mmol/L or any increase to a level above 5.5 mmol/L. All significant increases in plasma creatinine are evaluated by study investigators, and in case of doubt of the etiology, the study drug is discontinued until renal function has stabilized. All adverse events registered throughout participation in the study will be recorded. Serious adverse events are defined according to Good Clinical Practice as events that result in death, are life threatening, require hospitalization, cause prolongation of existing hospitalization or result in persistent or significant disability/incapacity. The project safety board continuously monitors serious adverse events to identify general study safety issues.

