### Withdrawal

Withdrawal criteria include a sustained compliance of less than 80%, hyperkalemia despite reduction of dosage or intolerable side effects.

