### Sample size

Assuming a standard deviation in chrome-EDTA clearance of 10 mL/min, a sample size of 126 patients (63 in each group) will be able to detect a difference in chrome-EDTA clearance of 5 mL/min between the groups with 80% power and a significance level of 0.05. With an expected dropout rate of 15%, the planned total was set to 170 patients.

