### Allocation and blinding

After completing the baseline workup (Fig. 1), patients are allocated to consecutive randomization numbers. Randomization has been performed by the pharmacy at Odense University Hospital in blocks of four. The allocation code is blinded to both patients and investigators and is solely known by the pharmacy. Opaque envelopes containing the individual allocation are available on site in case of the need for emergency unblinding. If the allocation code is revealed before completing the trial the patient will be excluded.

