### Statistical methods

All statistical analyses will be done using STATA software. All generated variables will be documented by do-files. The main analysis will be performed as intention-to-treat using last-observation-carried-forward. Sub-analyses will include per protocol analyses and “best case”/“worst case” analyses. Where appropriate, variables will be analyzed using parametric or non-parametric tests.

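### Last-observation-carried-forward is fixed as the main method with no exemption for cardiovascular events, so read as written it counts withdrawn patients as event-free for time nobody observed

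*Protocol article*

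**What the plan says.** The Outcome section of the protocol article lists among the secondary endpoints "cardiovascular events (death, myocardial infarction, stroke or peripheral arterial thrombosis"), without a time point or summary measure. Under Methods, "Patients are randomized 1:1 to spironolactone (Spirix®) or placebo for three years".

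The Statistical methods section gives one main rule for all data: "The main analysis will be performed as intention-to-treat using last-observation-carried-forward". It names no endpoint and excludes none. It then adds "Sub-analyses will include per protocol analyses and “best case”/“worst case” analyses", and leaves the choice between parametric and non-parametric tests to what suits each variable.

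Patients can leave early by several routes. The Withdrawal section says "Withdrawal criteria include a sustained compliance of less than 80%, hyperkalemia despite reduction of dosage or intolerable side effects". The Safety section shows that, for hyperkalemia, this means leaving the study and not only the drug: "In case of hyperkalemia on 25 mg per day, the patient will be withdrawn from the study". Allocation and blinding adds "If the allocation code is revealed before completing the trial the patient will be excluded". The Sample size section states "With an expected dropout rate of 15%, the planned total was set to 170 patients", with no split by arm.

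Adverse events are assessed at three-monthly project visits (Methods, text below Table 2), and the Safety section describes their recording as covering the period of participation. The article mentions no follow-up of events or vital status after withdrawal.

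**The concern.** Carry-forward is built for a measurement taken repeatedly, such as chrome-EDTA clearance. An event composite has no last value in that sense. Its last observation in a patient who leaves at month 6 without an event is simply no event so far. Carrying that to year 3 credits the patient with up to two and a half event-free years that were never observed.

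Two consequences follow. The event risk is too low in both arms. In addition, the arm with more withdrawals, or earlier ones, has its risk lowered more, which looks like a benefit. Two of the three withdrawal criteria, hyperkalemia and intolerable side effects, are plausibly linked to the active drug. The Discussion itself treats hyperkalemia as a known risk of this drug class. Because the composite includes death, even a modest distortion in favor of the study drug is unwelcome.

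**Working it through.** **Inputs from the protocol article.** Follow-up of 3 years; 170 patients randomized 1:1, so 85 per arm; overall dropout 15%, i.e. 0.15 × 170 = 25.5, about 26 patients. The article states no figure for cardiovascular events, so there is none to reproduce.

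**Assumptions, not in the article.** A constant event rate h, the same in both arms (no true effect): 4% per year, varied from 2% to 6%. Dropout by arm: 15%/15%, 20%/10% or 25%/5% (spironolactone/placebo), each averaging the stated 15%. Dropout times are spread evenly over 0–3 years or over the first 6 months. Dropout is unrelated to event risk.

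**Formulas.**
- True 3-year risk: F = 1 − exp(−3h).
- Mean risk up to dropout, for dropout times even on 0 to T: m = 1 − [1 − exp(−hT)]/(hT).
- Proportion under carry-forward with dropout share d: p = (1 − d)F + d·m.

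**Values at h = 0.04.** F = 1 − exp(−0.12) = 0.1131. For T = 3, m = 1 − 0.1131/0.12 = 0.0577. For T = 0.5, m = 1 − 0.0198/0.02 = 0.0099.

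**Understatement with equal dropout of 15%, even over 3 years.** p = 0.85 × 0.1131 + 0.15 × 0.0577 = 0.1048, against a true 0.1131. That is about 7% too low in each arm, and the risk ratio is 1.00.

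**Unequal dropout, h = 0.04.**

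| Dropout (spironolactone/placebo) | Timing | Proportions | Spurious risk ratio | Difference in events, 85 per arm |
|---|---|---|---|---|
| 20%/10% | even over 3 years | 0.1020 / 0.1075 | 0.95 | 0.5 |
| 20%/10% | first 6 months | 0.0925 / 0.1028 | 0.90 | 0.9 |
| 25%/5% | even over 3 years | 0.0992 / 0.1103 | 0.90 | 0.9 |
| 25%/5% | first 6 months | 0.0873 / 0.1079 | 0.81 | 1.8 |

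For example, row one: 0.80 × 0.1131 + 0.20 × 0.0577 = 0.1020; 0.90 × 0.1131 + 0.10 × 0.0577 = 0.1075; ratio 0.95. The ratios barely change at 2% or 6% per year.

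**Size against sampling error.** The standard error of the log risk ratio is √[(1 − p₁)/(85p₁) + (1 − p₂)/(85p₂)]. In the last row it is 0.469, and ln(0.809) = −0.212, so the bias is 0.45 standard errors. Over all unequal scenarios and 2–6% per year, the bias runs from 0.08 to 0.56 standard errors.

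**What best-case/worst-case analysis would show.** Treat event status as missing for everyone who withdraws, and take spironolactone minus placebo at F = 0.1131. With 15%/15%, the observed parts cancel and the bounds are −0.15 to +0.15. With 20%/10%, the best case is 0.0905 − (0.1018 + 0.10) = −0.11 and the worst case is (0.0905 + 0.20) − 0.1018 = +0.19. Both ranges contain the carry-forward bias, but they are far too wide to serve as an estimate.

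**The case against.** The strongest objection is that carry-forward may never have been meant for events. The sentence speaks of the main analysis, the sole primary endpoint is a yearly measurement, and tests are to be chosen per variable; a log-rank test is itself non-parametric. This is a fair reading and cannot be excluded. But the sentence carries no such limit, so an analyst following it literally would apply it to every endpoint. What stands is a need to restrict the wording, not proof of an intended misuse.

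A reader might also infer more than the article supports:

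- *That carry-forward is the only rule for missing data.* It is not. Per-protocol and best-case/worst-case sub-analyses are planned, and the latter bound this very bias. They remain sub-analyses.
- *That withdrawn patients cannot be scored.* Events before withdrawal are picked up at the three-monthly visits, and later follow-up is unmentioned but not ruled out.
- *That the composite is defined as a 3-year proportion.* The horizon comes from the trial's duration; the Outcome section gives none.
- *That spironolactone would appear protective.* This needs unequal withdrawal, which is not quantified. The Discussion also cites a safety study of 31 transplant patients on eplerenone with no withdrawals for hyperkalemia. That study lasted 8 weeks at 25 mg/day of a different drug, so it is weak reassurance for 3 years, but it does count against assuming a large imbalance.
- *That the lack of a named time-to-event method is a fault.* A condensed article may leave this to an analysis plan that is not shown.

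**Conclusion.** The point holds in a limited form. The article fixes carry-forward as the main method without exempting the cardiovascular composite, while treatment-linked criteria take patients out of the study and event recording is described only during participation. Followed literally, this understates event risk in both arms, and it biases the comparison toward spironolactone only if withdrawal is higher or earlier there. The calculated risk ratios depend on an assumed event rate and an assumed split of dropout; only the 15% average is the plan's. The largest distortion, 0.81, needs 25% versus 5% dropout, all within six months. Even the largest shift, about 0.6 of a standard error at 6% events per year, moves the estimate more than the test. This is a minor matter on a secondary endpoint, worth correcting because the correction is cheap.

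**What to change.** In the Statistical methods section:

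1. Restrict carry-forward, where it is kept, to repeated measurements, and state that it does not apply to cardiovascular events.
2. Analyze cardiovascular events as time from randomization to first event, with all randomized patients in their allocated arm and follow-up ending at the last date on which event status is known (hazard ratio from a Cox model, log-rank test).
3. Report person-years of observation per arm, so that any imbalance is visible.
4. Count deaths and events known from clinical records after withdrawal, up to 3 years from randomization.

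The first three steps change only wording, as the three-monthly adverse event records should supply the dates. The fourth needs some record review for the roughly 26 patients expected to drop out, as far as their consent allows. The remaining weakness is that censoring at dropout still assumes dropout is unrelated to event risk. The fourth step reduces reliance on that assumption, and the planned best-case/worst-case analyses can stay as bounds.

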### Safety

Plasma potassium and -creatinine levels are monitored closely at initiation of therapy and after any dose adjustment. Sustained potassium levels > 5.8 mmol/L will result in reduction of dosage to 25 mg per day. In case of hyperkalemia on 25 mg per day, the patient will be withdrawn from the study. Potassium binding resins will only be used to handle cases of acute hyperkalemia, thus chronic treatment with resins is not allowed. Hyperkalemia is registered as an adverse event in case of an absolute increase of > 1.5 mmol/L or any increase to a level above 5.5 mmol/L. All significant increases in plasma creatinine are evaluated by study investigators, and in case of doubt of the etiology, the study drug is discontinued until renal function has stabilized. All adverse events registered throughout participation in the study will be recorded. Serious adverse events are defined according to Good Clinical Practice as events that result in death, are life threatening, require hospitalization, cause prolongation of existing hospitalization or result in persistent or significant disability/incapacity. The project safety board continuously monitors serious adverse events to identify general study safety issues.

